**Methods/design:**

A randomized controlled trial will be conducted to compare the booklet self-help program with coaching with an attention-only control condition, by including pre-test, post-test, and follow-up assessments. We aim to enroll 200 participants with mild to moderate depressive symptoms into the study. The self-help program contains the following main components: activation, relaxation, changing maladaptive cognitions, and the attainment of new personal goals. This content is covered over six lessons to be completed in a maximum of 8 weeks. It uses a combination of psycho-education, assignments, and exercises. The participants will work on the program 1–2 h every week for 6 weeks (maximum 8 weeks). Coaches will offer support and motivate the participants. For both groups, depressive symptoms and possible mediators will be measured three times during the intervention, and at pre-test, post-test, and follow-up.

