The pre-test, post-test, and follow-up assessments will be done by the researchers through a standardized telephone interview; the three assessments during the intervention will be done during the coaching sessions, after the completion of lessons 1 (activation), 2 (physical relaxation), and 4 (changing negative thinking patterns). Callers will follow a standard script where they will explain who they are and the purpose of the interview. Participants will be asked questions exactly as they appear on the questionnaire. The answer categories for each section will be called out, and the participants will be asked to write them down for easy reference. Callers are allowed to repeat questions at the request of the participant.

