### Study conditions: booklet self-help intervention

The booklet self-help with coaching intervention employs cognitive behavioral therapy (CBT) and stress management techniques and is based on self-regulation and stress-coping theories [28]. The content of the self-help program contains the following main components: activation, relaxation, changing maladaptive cognitions, and the attainment of new personal goals. This content is covered over six lessons to be completed in a maximum of 8 weeks and uses a combination of psycho-education, assignments, and exercises. To reduce attrition over time and to keep participants motivated, coaches will offer support and motivate participants.

The participants receive the intervention in the form of a booklet and will work on the program 1–2 h every week for 6 weeks. The first lesson is an introduction to the program and focuses on activation. Participants will be asked and encouraged to think of a small concrete new activity to perform. Throughout the program, participants will be encouraged to continue thinking about small concrete new activities to perform. Lesson 2 will be cover physical relaxation. Participants are taught to do some relaxation exercises that they continue with for the rest of the program. The third lesson will focus on changing negative thoughts. Participants are trained to recognize and change their negative thinking patterns. In lesson 4, participants will learn strategies to stop unpleasant thoughts whenever they want (for instance, by using a positive feeling). In lesson 5, participants will be helped to find new, meaningful, concrete, and time-bound life goals. They will be guided to work on attaining their goals. The last lesson will focus on achieving self-confidence to achieve their goals. Participants will learn to challenge negative thoughts which prevent them from working on their goals and gain confidence to achieve their goals. The program concludes with a summary of the important tips and tricks.

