### Support from a coach

A coach will be allocated to each participant to provide support and motivation for the duration of the program. At the beginning of the program, the coaches will make telephone contact with the participants to introduce and explain technical aspects of the program and provide motivation. The coach will also schedule a weekly telephone call with the participant that will last approximately 15 min. During the telephone call, the coach will enquire about the progress of the participant and problems encountered and will offer support and motivation as well as encourage the participant to continue working on the program. Coaches follow a script to interview patients. Furthermore, coaches will be asked to record their telephone calls and also note what they discussed with the patient after every call. The audio recording and notes will be used to check if the coach follows protocol during supervision with the researchers and/psychologist. No formal psychotherapy will be provided to the participants by the coaches. During the telephone calls, the coach will provide support and motivation by enquiring about the participant’s progress, making motivational statements, and listening and providing guidance in case the participant is facing any problems. Six telephone coaching sessions will be provided in total, connected to each of the six lessons. The participant is expected to complete the program in 6 weeks, with a maximum extension to 8 weeks. If a participant has not completed the program after 8 weeks, he/she is allowed to continue with the program; however, the coaching will stop.

In the control condition, all participants will only receive minimal support in the format of six telephone calls by a coach over a period of 6–8 weeks. The weekly telephone calls between coaches and participants in the control condition will last for approximately 5 min. During this telephone call, the coaches will enquire about the participant’s well-being. Coaches will monitor the depressive symptoms of the participants and try to prevent participant dropout by helping them to explore solutions to the obstacles they face with the program, discussing the pros and cons of quitting, and continuing to make motivational remarks.

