### Assessments

The data will be collected at six different times during the trial (T0, three in-between assessments during the intervention, T1, and T2). Table 1 shows each stage of the study and the assessments that will be used. The initial screening (PHQ-2) will be done at the treatment centers by HIV nursing staff and doctors. At T0, T1, and T2, the researchers will conduct the assessments via a standardized telephone interview. The three in-between assessments will be conducted by the coaches by telephone.

**Table 1 Tab1:** Summary of assessments for the study

Assessment	Screening HIV treatment centers *(+/− 5 min)*	Screening researchers *(+/− 10 min)*	T0: pre-test *(+/− 25 min)*	Three times during intervention/waiting period^1^ *(+/− 10 min)*	T1: post-intervention/waiting period: 6–8 weeks after T0^1^ *(+/− 20 min)*	T2: 3 months follow-up *(+/− 20 min)*
PHQ-2	X	–	–	–	–	–
PHQ-9	–	X	X	–	X	X
CES-D	–	–	X	–	X	X
Demographics and other information	–	–	X	–	X	X
Physical tension questionnaire	–	–	X	X	X	X
BADS	–	–	X	X	X	X
CERQ-short	–	–	X	X	X	X
Self-efficacy questionnaire	–	–	X	X	X	X
Goal Disengagement and Reengagement Scale	–	–	X	X	X	X
BERQ	–	–	X	–	X	X
GAD-7	–	–	X	–	X	X
PHQ-4	–	–	–	X	–	–
Life Events Scale	–	–	X	–	X	X
Motivation	–	–	X	–	–	–
Social support	–	–	X	–	X	X
Alcohol and substances	–	–	X	–	X	X
Compliance	–	–	–	X	X	–
Dropout	–	–	–	X	X	–
User satisfaction questionnaire	–	–	–	–	X	–

*PHQ-2* Patient Health Questionnaire 2, *PHQ-9* Patient Health Questionnaire 9, *CES-D* Center for Epidemiological Studies Depression Scale; BADS = Behavioral Activation for Depression Scale, *CERQ* Cognitive Emotion Regulation Questionnaire, *BERQ* Behavioral Emotion Regulation Questionnaire, *GAD-7* Generalized Anxiety Disorder 7, *PHQ-4* Patient Health Questionnaire 4

^1^Not asked to participants in the control group

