#### Dropout and reasons for dropout

We will take record of all participants who are no longer following the intervention and those who have no interest in completing the questionnaires. Participants are expected to complete questionnaires at three different points during the intervention/waiting period and at post-test. Participants will be asked the reason(s) for dropping out of the study.

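### The three in-between mediator and PHQ-4 assessments are triggered by lesson completion with no calendar time, so in the intervention arm their timing and missingness depend on adherence

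*Protocol article*

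**What the plan says.** **Trigger.** The Procedure section states that "the three assessments during the intervention will be done during the coaching sessions, after the completion of lessons 1 (activation"), and names lessons 2 and 4 as the other two triggers. The Assessments section adds: "The three in-between assessments will be conducted by the coaches by telephone".

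**Coach contact.** Under Support from a coach: "Six telephone coaching sessions will be provided in total, connected to each of the six lessons". The same section says "The coach will also schedule a weekly telephone call with the participant that will last approximately 15 min" and, on late finishers, "If a participant has not completed the program after 8 weeks, he/she is allowed to continue with the program; however, the coaching will stop".

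**Expected data.** The abstract says "For both groups, depressive symptoms and possible mediators will be measured three times during the intervention". The dropout section says "Participants are expected to complete questionnaires at three different points during the intervention/waiting period and at post-test". It also records people who no longer follow the intervention separately from people with no interest in completing questionnaires. The Compliance items, asked at the three points and at post-test, ask which lessons were done and offer an answer meaning none at all.

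**Use.** The Assessments section gives the purpose of the mediator measurements as showing which mechanisms come before change in the primary outcome. Statistical analyses names a latent difference score model for mediation.

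**Lesson labels.** The Procedure section describes lesson 4 as the one on changing negative thinking patterns. The description of the booklet says "The third lesson will focus on changing negative thoughts" and gives lesson 4 to stopping unpleasant thoughts.

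**The concern.** A measurement that takes place only once a participant has completed a task is conditional on adherence. Here the task exists in the intervention arm alone, since controls have no lessons during the comparison period. If the trigger is followed as written, the intervention participants scored at the in-between waves are those who progressed, while controls are scored without any such condition.

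People who progress may well be those whose activation, self-efficacy or coping is already better or improving. The arms could then differ on a mediator at these waves through selection, with no effect of the program on it. Timing has the same weakness: among those who are scored, elapsed time since randomisation varies with pace.

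At stake is the mediation aim. T0, T1 and T2 provide no wave inside the treatment period, so a statement about what changes first rests on these three waves.

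**Working it through.** **1. Is there a plan figure to reproduce?** Not on this point: the article gives no lesson-completion rate. Its only attrition figure is the 15% dropout in Sample size. There, 64 / (1 − 0.15) = 75.3, against the stated minimum of 75 per group. So the 15% is loss from the trial, applied to both groups. It is not the share of intervention participants who stay in contact but do not finish a lesson.

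**2. The rules side by side.**

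| Wave | What fixes its time | Depends on lessons? |
|---|---|---|
| T0 | before randomisation | no |
| Three in-between | completion of lessons 1, 2 and 4, at a coaching session | yes, intervention arm |
| T1 | 8 weeks, all participants (Procedure); 6–8 weeks after T0 (Table 1) | no |
| T2 | 3 months later | no |

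The in-between waves are the only ones without a calendar time. A participant who stops after lesson 2 and still takes the coach's calls meets no trigger for the third assessment. One who reaches lesson 4 after week 8 has no coaching session in which to be assessed.

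**3. Timing among those scored** (assumes an even pace).
- Six lessons in 6 weeks: 6/6 = 1 week per lesson, so the triggers fall at weeks 1, 2 and 4.
- Six lessons in 8 weeks: 8/6 = 1.33 weeks per lesson, so the triggers fall at weeks 1.3, 2.7 and 5.3.
- Two weeks per lesson: triggers at weeks 2, 4 and 8, the last falling as coaching stops.

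The third wave can thus lie anywhere from about week 4 to week 8, depending on pace.

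**4. How many might be unscored** (assumption only). With 100 in the intervention arm and a constant completion probability p per lesson, the number meeting the trigger after lesson k is 100·p^k.

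| p | After lesson 1 | After lesson 2 | After lesson 4 |
|---|---|---|---|
| 0.95 | 95 | 90 | 81 |
| 0.90 | 90 | 81 | 66 |
| 0.85 | 85 | 72 | 52 |
| 0.80 | 80 | 64 | 41 |

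**5. Shift in the observed mean** (assumption only). Let a share q of the intervention arm be unscored because of low progress, let progress and the mediator be bivariate normal with correlation r, and let the program have no effect on the mediator. The mean among those scored shifts by

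r · φ(z_q) / (1 − q), in SD units, where z_q is the q-quantile of the standard normal.

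- q = 0.15: φ(−1.036) = 0.233; 0.233/0.85 = 0.274. Shift 0.082 (r = 0.3) to 0.137 (r = 0.5).
- q = 0.25: φ(−0.674) = 0.318; 0.318/0.75 = 0.424. Shift 0.127 (r = 0.3) to 0.212 (r = 0.5).

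A wider range for the wave after lesson 4, with r from 0.1 to 0.5, gives 0.03–0.17 SD at 81% assessed and 0.09–0.47 SD at 41% assessed. All of these are raw shifts. Likelihood estimation that includes T0 and T1 mediator scores removes the part those scores explain.

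**6. Lesson label.** Procedure fixes the third trigger by number as lesson 4, but labels it with content that the booklet description gives to lesson 3.

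**The case against.** The strongest case against is that the article already foresees these people.

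- **Weekly calls continue for a stalled participant.** The dropout section expects three questionnaires, and the Compliance items have an answer for lessons not done. A reader might infer from the trigger that non-adherers cannot be scored at all; these sections do not support that. What stands is narrower: they expect data that the trigger does not secure, and no rule tells the coach when to collect them.
- **Most mediator data are not tied to lessons.** In Table 1, physical tension, activation, cognitive coping, self-efficacy and goal reengagement are also taken at T0, T1 and T2, by the researchers. A reader might infer that the intervention arm's mediator data come from adherers in general; that is not so. Someone not through lesson 4 by week 8 is still due the same mediators at T1. What may be lost is the wave inside the treatment period.
- **Tying assessments to lessons is a reasoned choice.** It places each measurement just after the matching component. This stands, and is why the fix keeps the lesson trigger and adds a backstop.
- **A journal article condenses.** Coach guidelines exist outside it and may hold a rule for missed triggers. That is possible. But the article does state the trigger, and it fixes T1 by calendar, so this is a stated rule and not a mere silence.
- **The label mismatch has an ordinary reading.** Lessons 3 and 4 can be taken as one cognitive block that closes with lesson 4. This largely stands, so it is a labelling point.

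**Conclusion.** The point holds for the three in-between waves. As written, their observation and timing in the intervention arm depend on adherence after randomisation, and participants who stall or stop the lessons but would still answer have no defined assessment time. This can bias the between-arm mediator comparison in the latent difference score analysis. The primary outcome and the T0, T1 and T2 mediator scores are untouched.

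The size is not known. The figure of about 0.08–0.21 SD rests wholly on assumed inputs: 15–25% unscored in the intervention arm only, a correlation of 0.3–0.5, no true effect on the mediator, and no recovery from other waves. The direction, too, assumes that progress goes with better mediator scores.

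Two further inferences are not supported. The 15% trial dropout should not be read as the unscored rate: it applies to each group, and people who have left the trial would be unscored under any schedule. Nor should the shift be turned into a false-positive rate through a simple two-group test of complete cases, because that is not the planned model.

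The conclusion takes controls to be assessed during the waiting period, as the abstract and the Assessments text say. A footnote to Table 1, attached to the in-between and T1 columns, says some content is not asked of controls; that is a separate matter to reconcile.

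**What to change.** In Procedure, state that each in-between assessment is done after the named lesson or at a fixed week counted from randomisation, whichever comes first, at the existing weekly call and whether or not the lesson has been done. Record the date and the lesson reached each time, and use time since randomisation in the mediation model. Reconcile the label of lesson 4 in Procedure with the booklet description, so that the third trigger has one meaning.

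The cost is a change of wording and a few assessments of about 10 minutes in calls that are largely scheduled already. The article says recruitment has not started, so the change can still cover everyone; in-between scores not collected at the time cannot be recovered later. The downside is small: some slow participants will be scored before the matching lesson, which the recorded lesson number will show.

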### Study conditions: booklet self-help intervention

The booklet self-help with coaching intervention employs cognitive behavioral therapy (CBT) and stress management techniques and is based on self-regulation and stress-coping theories [28]. The content of the self-help program contains the following main components: activation, relaxation, changing maladaptive cognitions, and the attainment of new personal goals. This content is covered over six lessons to be completed in a maximum of 8 weeks and uses a combination of psycho-education, assignments, and exercises. To reduce attrition over time and to keep participants motivated, coaches will offer support and motivate participants.

The participants receive the intervention in the form of a booklet and will work on the program 1–2 h every week for 6 weeks. The first lesson is an introduction to the program and focuses on activation. Participants will be asked and encouraged to think of a small concrete new activity to perform. Throughout the program, participants will be encouraged to continue thinking about small concrete new activities to perform. Lesson 2 will be cover physical relaxation. Participants are taught to do some relaxation exercises that they continue with for the rest of the program. The third lesson will focus on changing negative thoughts. Participants are trained to recognize and change their negative thinking patterns. In lesson 4, participants will learn strategies to stop unpleasant thoughts whenever they want (for instance, by using a positive feeling). In lesson 5, participants will be helped to find new, meaningful, concrete, and time-bound life goals. They will be guided to work on attaining their goals. The last lesson will focus on achieving self-confidence to achieve their goals. Participants will learn to challenge negative thoughts which prevent them from working on their goals and gain confidence to achieve their goals. The program concludes with a summary of the important tips and tricks.

### Support from a coach

A coach will be allocated to each participant to provide support and motivation for the duration of the program. At the beginning of the program, the coaches will make telephone contact with the participants to introduce and explain technical aspects of the program and provide motivation. The coach will also schedule a weekly telephone call with the participant that will last approximately 15 min. During the telephone call, the coach will enquire about the progress of the participant and problems encountered and will offer support and motivation as well as encourage the participant to continue working on the program. Coaches follow a script to interview patients. Furthermore, coaches will be asked to record their telephone calls and also note what they discussed with the patient after every call. The audio recording and notes will be used to check if the coach follows protocol during supervision with the researchers and/psychologist. No formal psychotherapy will be provided to the participants by the coaches. During the telephone calls, the coach will provide support and motivation by enquiring about the participant’s progress, making motivational statements, and listening and providing guidance in case the participant is facing any problems. Six telephone coaching sessions will be provided in total, connected to each of the six lessons. The participant is expected to complete the program in 6 weeks, with a maximum extension to 8 weeks. If a participant has not completed the program after 8 weeks, he/she is allowed to continue with the program; however, the coaching will stop.

In the control condition, all participants will only receive minimal support in the format of six telephone calls by a coach over a period of 6–8 weeks. The weekly telephone calls between coaches and participants in the control condition will last for approximately 5 min. During this telephone call, the coaches will enquire about the participant’s well-being. Coaches will monitor the depressive symptoms of the participants and try to prevent participant dropout by helping them to explore solutions to the obstacles they face with the program, discussing the pros and cons of quitting, and continuing to make motivational remarks.

The coaches will follow guidelines on the protocol regarding provision of support and motivation. All coaches will be trained in the study procedures, and they will be expected to record each telephone call conversation and the elements used during the call such as motivation and support. Coaches will be students with a minimum of a Bachelor of Psychology degree and will have completed a clinical course during their training and been taught communication skills, interview techniques, and treatment strategies. Personal interviews will be held before coaches are appointed, and only those coaches with adequate communication skills and the capacity to provide support and motivation will be selected. Selected coaches will be provided with extra training, such as motivational interviewing skills. The researchers and a licensed psychologist will supervise the coaches. In the first month of the study, the main researcher and the coaches will hold meetings every week to discuss any challenges they are facing. Thereafter, meetings will be held every 2 weeks. Should problems arise during meetings between the coaches and the main researcher, the responsible psychologist will be contacted.

### Ethical precautions

Coaches will monitor the depressive symptoms of all participants on a weekly basis by asking how the participants are doing. When participants express severe depressive symptoms, the PHQ-9 will be administered. In case of any participant in either condition showing severe depressive symptoms (PHQ-9 > 20) or suicide ideation, the coaches will follow referral guidelines. The coaches will discuss the situation with the participant before any steps are taken. The coaches will also discuss all steps with the psychologist. The participant can be referred to a medical doctor, his/her general practitioner, or the HIV treatment center. A participant who is referred for intensive treatment to a psychologist or psychiatrist may continue with the study. However, in the analysis, the referral will be entered as a covariate to account for the influence of the treatment. These guidelines are contained in the study protocol for coaches.

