### Participants

We will recruit about 200 participants from six HIV treatment centers in Botswana. These treatment centers were selected strategically to include the two largest referral hospitals serving the northern and southern ends of Botswana. As referral hospitals, they service PLH from different parts of the country, thus giving the study an increased likelihood of recruiting participants from various backgrounds.

Recruitment of participants will be conducted using a short initial screening during their regular visits to the HIV medical staff. Further screening will be done by the researchers. The inclusion criteria for participation in the study are as follows: being HIV positive, presenting with mild to moderate depressive symptoms (that is, a score greater than 4 and less than 20 on the Patient Health Questionnaire 9 (PHQ-9) [26], aged 18 years and older, having sufficient knowledge of the Setswana or the English language, and available for the next 8 weeks to work on the intervention. The exclusion criteria are as follows: (almost) no symptoms of depression (a score of 4 or less on the PHQ-9), presenting with severe cognitive impairments (medical staff and coaches to use their clinical judgement to determine if the patient may be presenting with severe cognitive deficits), being in the first 6 months post-HIV diagnosis, and suicidality as determined by a score of > 1 on the suicide item of the PHQ-9. Those who score within the severe depressive symptoms range (≥ 20) or suicide ideation as measured by the PHQ-9 will be referred for face-to-face psychological or psychiatric treatment or to a medical doctor at the treatment center.

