**Fig. 1 Fig1:**
[figure not shown]
Flowchart of the study design

In Botswana, the majority of patients who have been on treatment for more than a year visit the treatment center once every 6 months; therefore, the screening will be conducted over a period of approximately 6 months. Any patient who obtains a score > 0 on the PHQ-2 and who meets the inclusion criteria may be referred to the researchers. The HIV consultants will provide written information about the study to the patients and request for permission to provide the researchers with the patient’s contact information (telephone number or email). Following contact with the patients, the researchers will provide further information to the patients and conduct extensive screening for depressive symptoms using the PHQ-9 by telephone. Patients with a score within the mild (> 4) and moderate (< 20) ranges will be eligible for participation in the trial. These patients will then be invited to participate. Those who agree to participate will give consent by a text message to the researchers. Additionally, we will seek permission from patients to inform a medical doctor or general practitioner at the HIV treatment center about their participation in the study. Participants will then undergo a pre-test (T0). Thereafter, the participants will be randomly assigned to the intervention or the control (attention-only) group. The coaches will call all participants at the beginning of the intervention to assess for and stimulate their motivation. This will be accomplished through the use of motivational interviewing and general conversational techniques, providing information about the program, helping the patients plan for the lessons, and advising them to engage in a small activity to get started.

The intervention group will then receive the self-help treatment program with coaching by telephone, while the control group will only receive attention through a weekly telephone chat from a coach. The participants will work on the intervention for 6 weeks (with a maximum extension of 2 weeks). During the intervention, participants will be asked to answer standardized questions at three different times. At 8 weeks, all participants will complete the post-test (T1) and subsequently the follow-up measurement (T2) 3 months later. After the follow-up, participants in the control condition will receive the intervention.

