#### Patient Health Questionnaire 9 (PHQ-9)

The PHQ-9 will be used to measure the severity of the participants’ depressive symptoms during pre-test and post-tests [26]. It will be used for screening and for measuring change in depressive symptoms over the period of the intervention/waiting period. The questionnaire has nine items measured on a 4-point scale ranging from 0 (not at all) to 3 (nearly every day). The total score ranges from 0 to 27 with a score of ≤ 4 indicating minimal or no depressive symptoms, 5–9 mild depressive symptoms, 10–14 moderate depressive symptoms, 15–19 moderately severe depressive symptoms, and 20–27 severe depressive symptoms. A total score is obtained by adding the scores of the nine items. The scale has been widely used in measuring depressive symptoms and has good psychometric properties [26]. In addition, the PHQ-9 is often used with PLH and has been found to be highly reliable [37].

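### The in-trial referral trigger for severe depressive symptoms is printed as PHQ-9 > 20, but the trial's own severe range starts at 20

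*Protocol article*

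**What the plan says.** Four places in the protocol article put a number on the boundary of severe depressive symptoms.

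- **Ethical precautions** (during the trial): "In case of any participant in either condition showing severe depressive symptoms (PHQ-9 > 20) or suicide ideation, the coaches will follow referral guidelines". The PHQ-9 used for this is not routine: "When participants express severe depressive symptoms, the PHQ-9 will be administered".
- **Patient Health Questionnaire 9 (PHQ-9)** (definition of the bands): "15–19 moderately severe depressive symptoms, and 20–27 severe depressive symptoms".
- **Participants** (at entry): eligibility requires "a score greater than 4 and less than 20 on the Patient Health Questionnaire 9", and "Those who score within the severe depressive symptoms range (≥ 20) or suicide ideation as measured by the PHQ-9 will be referred".
- **Procedure**, text after Fig. 1 (eligibility restated): "Patients with a score within the mild (> 4) and moderate (< 20) ranges will be eligible for participation in the trial".

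Ethical precautions adds two points that bear on the rule in practice: "The coaches will also discuss all steps with the psychologist", and "These guidelines are contained in the study protocol for coaches".

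**The concern.** The same label on the same instrument carries two different numbers. Ethical precautions places severe symptoms above 20. The instrument description and the Participants section place them at 20 and above. Entry referral and in-trial referral are separate decision points, and a protocol may set different cut-offs for them. Here, however, the figure in Ethical precautions is given as the meaning of severe, not as a separate in-trial threshold, and nothing in the article explains a higher bar after randomization.

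What is at stake is participant safety. The Discussion says that patients in the severe range need more intensive care than the booklet offers, and the trial refers and excludes a score of 20 at entry. As printed, a participant who reaches that same score during the trial does not meet the numeric trigger. The people applying the rule are coaches, who are psychology students with at least a bachelor's degree and who work by telephone from a script. For them the exact number matters.

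**Working it through.** No sample-size or power calculation is involved. The check enumerates PHQ-9 totals against each printed rule.

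**Inputs.** The PHQ-9 section gives nine items scored 0 to 3, summed. Totals are therefore whole numbers from 0 to 9 × 3 = 27, and > 20 means 21 or more.

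| Rule | Section | Scores covered | Count |
|---|---|---|---|
| Severe band | Patient Health Questionnaire 9 (PHQ-9) | 20–27 | 27 − 20 + 1 = 8 |
| Referral at entry, ≥ 20 | Participants | 20–27 | 8 |
| Eligible, > 4 and < 20 | Participants; Procedure | 5–19 | 15 |
| In-trial referral, > 20 | Ethical precautions | 21–27 | 27 − 21 + 1 = 7 |

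**Comparison.**

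1. The severe band and the entry-referral set are identical, and the eligible range stops immediately below them. These rules agree on a boundary at 20.
2. Severe band minus in-trial trigger: {20–27} − {21–27} = {20}. One of eight severe scores is left out (1/8 = 12.5% of score values, which is not a share of participants).
3. For a participant who enters at the ceiling of 19, the severe band is reached after a rise of 20 − 19 = 1 point, but the printed trigger only after 21 − 19 = 2 points.
4. With the trigger at ≥ 20, the in-trial set becomes {20–27}. It then equals both the severe band and the entry-referral set, and no severe score falls below the trigger.

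The article gives no distribution of PHQ-9 scores among participants who would be given the questionnaire under this rule, so a count of people affected cannot be computed.

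**The case against.** The mismatch in print is hard to dispute. The case on the other side concerns its weight.

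- **Coaches work from another document.** The referral guidelines are in a coaches' protocol that is not shown and may print ≥ 20. This stands: it is not established that a score of 20 would go unreferred in practice. It is a reason to check that document and does not correct the figure printed here.
- **The number may be only a gloss.** The sentence turns on a participant showing severe symptoms, with the figure in parentheses. Since the term is defined elsewhere as 20–27, a reader could let the definition prevail and treat the figure as a slip for ≥ 20. That is probably how it arose, and nothing suggests that anyone chose 21 over 20. A safety rule should still not depend on the reader resolving a contradiction.
- **Exposure is narrow.** The gap needs a participant who has already voiced severe symptoms, then scores exactly 20, and reports no suicide ideation, which is a separate trigger. Coaches ask about symptoms weekly, and the researchers and a licensed psychologist supervise them. This stands and limits the harm. Discussing steps with the psychologist is a weaker safeguard than it looks, because it may apply only once referral is already under consideration.
- **The trial's inference is hardly affected.** This also stands. The only analytic link is that referral for intensive treatment is to be entered as a covariate, and the effect of one score value on that covariate cannot be quantified.

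**Conclusion.** The concern holds. The in-trial trigger of > 20 contradicts the article's own definition of severe symptoms and its entry referral rule, and it errs in the less protective direction. The discrepancy is exactly one score value, 20. The conclusion rests on the printed text and on PHQ-9 totals being whole numbers, and needs no distributional assumption. Two things remain unknown: how many participants would land on that score, and which figure the coaches actually use. This is a narrow internal inconsistency in a safety threshold that should be corrected. It does not threaten the trial's main analysis.

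**What to change.** In Ethical precautions, change the trigger from PHQ-9 > 20 to PHQ-9 ≥ 20. Check that the coaches' protocol and any script derived from it carry the same figure.

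The cost is one symbol and one check. A few more participants might be referred, but the article allows those referred for intensive treatment to stay in the study, so retention need not suffer. According to Trial status, recruitment had not begun, so the change could be made before it affects anyone.
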